
### Participant timeline

2.5

A flowchart of participant timeline is shown in Figure 2.

**Figure 2 F2:**
[figure not shown]
Participant timeline. AE & SAE = adverse events & serious adverse events, CCIS = Cleveland clinic incontinence score, H&P = history and physical examination, LARS = low anterior resection syndrome (questionnaire), QLQ-C30 = quality-of-life questionnaire core 30, QoL = quality of life, SF-36 = short form (36 item), VAS = visual analog scale.

### Sample size

2.6

Considering that this is a noninferiority study, the sample size was calculated using 1-sided Blackweder test.^[15]^ According to published data, the incidence of colorectal anastomotic leakage formed standard DST varies from 7% to 25%.^[16]^ Colorectal AL rate after LAR with preventive stoma formation at the study center averages at 18%. The expected incidence of colorectal AL after 3-row suturing device is 30%. The purpose of this study is to obtain preliminary results demonstrating that the outcomes of colorectal anastomosis formation with a 3-row suturing device are noninferior compared to those of a 2-row suturing device. Considering that *α* = 0.05; the statistical power of the study is 80%; the patients are randomized into 2 groups with 1:1 allocation ratio; the noninferiority margin Δ = 5%, the required sample size is 154 patients (77 patients in each of the 2 groups). Thus, if there is a true difference in favor of the experimental treatment of 12% with respect to AL rate, then 154 patients are required to be 80% sure that the upper limit of a 1-sided 95% confidence interval will exclude a difference in favor of the standard group of more than 5%.

In order to conduct an interim analysis to assess the safety of 3-row suturing devices for the formation of a colorectal anastomosis, 20 patients will be included in each group. Given a 10% probability of patients leaving the study, it is necessary to recruit 22 patients in each group. Thus, a sample of 44 patients (22 in each of the 2 comparison groups) should allow for a reliable preliminary assessment of the safety and feasibility of the use of 3-row suturing devices for the formation of colorectal anastomosis.

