**Methods::**

The THREESTAPLER trial (Clinical Trials NCT03910699) is a prospective, noninferiority, 2-armed, parallel-group, patient and outcomes assessor blinded study with a 1:1 allocation ratio. Colorectal anastomosis will be formed using Ethicon 29 mm Curved Intraluminal Stapler (CDH29A) in the active comparator group, and using Mirus Disposable Circular Stapler 3 Row 29 (MCS-29R3) in the experimental group. The hypothesis states that the incidence of AL in the 3-row stapler group is at least not higher than in the 2-row stapler group. Assuming there is a difference in success rate of 12% and noninferiority margin Δ = 5%, 154 patients will be required to achieve statistical significance. An interim analysis will be performed after recruitment of 20 patients per group to assess safety profile of 3-row circular staplers. The primary endpoint is the rate of AL, documented by imaging studies, assessed with Pearson Chi-squared test and Fisher exact test. The secondary outcomes include severity of AL (A, B, or C), anastomotic bleeding, postoperative complication rate graded with the Clavien–Dindo classification, reintervention rate, stapler dysfunction rate, complications of defunctioning stoma, overall and cancer-specific quality of life, assessed with short form (36) and quality-of-life questionnaire core 30 questionnaires, respectively, fecal incontinence assessed with Cleveland clinic incontinence score form, and manifestation of LAR syndrome. All patients will be monitored for 12 months following the LAR.

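### Section 2.6 expects the 3-row stapler to leak 12 points more than the centre's rate, yet bases 154 patients and 80% power on a 12-point difference in its favour

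*Protocol article*

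**What the plan says.** All the inputs stand in the first paragraph of section 2.6 (Sample size) of the protocol article.

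- Centre's rate: "Colorectal AL rate after LAR with preventive stoma formation at the study center averages at 18" per cent.
- 3-row rate, in the next sentence: "The expected incidence of colorectal AL after 3-row suturing device is 30" per cent.
- Basis for the sample size, at the end of the paragraph: "Thus, if there is a true difference in favor of the experimental treatment of 12% with respect to AL rate", 154 patients give 80% assurance that "the upper limit of a 1-sided 95% confidence interval will exclude a difference in favor of the standard group of more than 5" per cent.
- Method: "the sample size was calculated using 1-sided Blackweder test", with alpha 0.05, 80% power, 1:1 allocation, a 5% margin and 77 patients per group.
- Published range for leakage with the standard double-stapling technique: 7% to 25%.

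The Methods part of the abstract has "Assuming there is a difference in success rate of 12" per cent, with the same margin and the same 154 patients. It does not say which device the difference favours.

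**The concern.** Leakage is the harm. A move from 18% to 30% is a deterioration of 12 points, more than twice the margin, so on those two rates the noninferiority hypothesis is false. The closing sentence assumes the reverse. The power claim for the primary endpoint therefore rests on inputs that contradict each other.

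Two things are at stake. First, a reader cannot tell what the 80% power is conditional on. Second, the primary objective in section 1.2 is only to show that 3-row leakage is not more than 5 points higher. If the true benefit is much smaller than 12 points, the trial can fail to show noninferiority for lack of patients, and that failure could be misread as evidence against the device.

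**Working it through.** **Inputs (section 2.6).** One-sided alpha 0.05 (z = 1.645), power 80% (z = 0.842), margin 0.05, 77 per arm, rates of 18% and 30%. Section 2.6 does not tie the 18% to a device by name. I take it as the 2-row rate, because section 1.1 describes the 2-row stapler as the one conventionally used for over 10 years.

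**Formulas** (normal approximation, unpooled variance; pC = 2-row leak rate, pE = 3-row leak rate):

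- n per arm = (1.645 + 0.842)² × [pC(1 − pC) + pE(1 − pE)] / [0.05 − (pE − pC)]²
- power = Φ( [0.05 − (pE − pC)] / SE − 1.645 ), with SE = √{[pC(1 − pC) + pE(1 − pE)] / n}

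**Step 1: reproduce the plan.** Take pC = 0.30 and pE = 0.18. The variance sum is 0.2100 + 0.1476 = 0.3576 and the distance to the margin is 0.05 + 0.12 = 0.17.

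- n = 6.18 × 0.3576 / 0.0289 = 76.5, so 77 per arm and 154 in total.
- SE = √(0.3576 / 77) = 0.0681; power = Φ(0.17 / 0.0681 − 1.645) = Φ(0.85) = 80.2%.

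This matches the stated figures.

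**Step 2: a second route to the same number.** Suppose 18% (2-row) and 30% (3-row) keep their labels but are entered as success rates. The variance sum is again 0.1476 + 0.2100 = 0.3576. The 3-row arm is now 12 points better, so the distance to the margin is again 0.17 and n is again 76.5, or 77. This route fits the abstract, which describes the 12% as a difference in success rate. The arithmetic therefore cannot tell exchanged labels from a leak rate entered as a success rate.

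**Step 3: the rates as labelled.** Take pC = 0.18 and pE = 0.30. The distance to the margin is 0.05 − 0.12 = −0.07.

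- Power at 77 per arm = Φ(−0.07 / 0.0681 − 1.645) = Φ(−2.67) = 0.4%.
- Because the true difference lies beyond the margin, a larger trial only lowers this probability. No sample size gives 80%.

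**Step 4: other pairs that keep the centre's 18% as the 2-row rate.**

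| 2-row | 3-row | Power at 77 per arm | n per arm for 80% |
|---|---|---|---|
| 18% | 6% (12 points better) | 95.1% | 6.18 × 0.2040 / 0.0289 = 43.6, so 44 |
| 18% | 8% | about 88% | not computed |
| 18% | 10% | about 76% | not computed |
| 18% | 12% | about 61% | not computed |
| 18% | 18% (no difference) | 20.1% | 6.1826 × 0.2952 / 0.0025 = 730.04, so 731 |

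Simulating the one-sided 95% upper limit at 77 per arm gives 79.9% for 30%/18%, 0.4% for 18%/30% and 20.2% for 18%/18%, in line with the formula.

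**Step 5: is either route to 77 supported as a control rate?** Step 1 needs a 2-row leak rate of 30%. That is above the centre's 18%, above the cited 7% to 25%, and above the 6.3%, 12.3%, 11% and 10.0% quoted in section 1.1. Step 2, taken at face value, implies a 2-row leak rate of 100% − 18% = 82% and a 3-row rate of 70%, which nothing in the document supports.

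**The case against.** The strongest defence is that 154 is not a miscalculation. It follows from the closing sentence: 12 points in favour of the 3-row device, a 5-point margin, one-sided 0.05, and the 18%/30% pair. On that view one sentence is mislabelled and the sample size is sound. The first half of this stands: the formula was applied correctly. The second half does not. Relabelling restores the arithmetic but leaves a 30% control rate with no support in the document.

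A second defence is that assuming a true benefit in a noninferiority design is legitimate, so the plan cannot be faulted for low power under equal rates. That also stands. The 18%/18% case is a sensitivity scenario, not an assumption of the plan. Applying the plan's own 12-point benefit to the centre's 18% gives 154 patients more power than claimed (95%).

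Third, section 2.6 and the Discussion already describe the aim as preliminary. This softens the consequence, but the same paragraph still claims 80% power for a noninferiority conclusion.

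**Conclusion.** The point holds as an internal contradiction about direction, and possibly about scale, in the inputs to the primary sample size. As labelled, the rates give about 0.4% power at 77 per arm, against a stated 80%. These figures assume that the 18% is the 2-row leak rate and that the usual unpooled normal approximation was used. That approximation reproduces 77 per arm.

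A reader might infer three stronger things, which the document does not support:

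- That the two rates were certainly attached to the wrong arms. Treating leak rates as success rates gives the same 77, and nothing in the text decides between the two.
- That the authors really expect a device that is worse by more than the margin. The closing sentence says the opposite.
- That the trial's power is 20%. That holds only if both devices leak at 18%.

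**What to change.** In section 2.6:

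- State the assumed AL rate for each device by name, on one scale (leak or success), the direction in which the 12 points run, and the basis for the control rate.
- Restate the power of 154 patients under the corrected inputs: about 80% if 2-row is 30% and 3-row 18%; about 95% if 18% and 6%. Add as a sensitivity case about 20% if both are 18%, where about 731 per arm would be needed for 80%.
- If a 12-point benefit cannot be justified, say that the trial yields a preliminary estimate with a confidence interval, and not a noninferiority test with 80% power.

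In the abstract, add the direction of the 12% difference; as it stands it is incomplete rather than wrong.

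The cost is rewording and one recalculation. No extra patients are needed. The downside is that the stated power may become less favourable.

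### The 10% attrition allowance is applied to the interim sample but not to the main 154, so the stated 80% power holds only if every patient has an evaluable primary outcome

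*Protocol article*

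**What the plan says.** The protocol article, section 2.6 (Sample size), sets 80% power, α of 0.05 and a 5-point noninferiority margin, and concludes that "the required sample size is 154 patients (77 patients in each of the 2 groups"). The calculation is described as one-sided, and the success criterion is a one-sided 95% upper confidence limit that excludes the margin. No allowance for loss is mentioned beside the 154.

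The next paragraph of the same section turns to the interim sample of 20 per group: "Given a 10% probability of patients leaving the study, it is necessary to recruit 22 patients in each group". No other attrition figure appears in the article.

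The Methods part of the abstract repeats the main number: "154 patients will be required to achieve statistical significance".

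Four other sections bear on who has an evaluable outcome:

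- Section 2.2 lists, as postoperative exclusions, patients who cannot complete the trial procedures, who die early of causes other than a leak, or who withdraw.
- Section 2.4.1 closes the primary window at stoma reversal, usually 4 to 6 weeks after surgery. Patients without symptoms have their leak status established by a contrast X-ray before reversal.
- Section 2.9.1 says that data collected before a patient exits will be analysed, and section 2.9.3 states intention to treat.
- Section 2.9.4 places the interim after 20 patients per group have completed 3 months of follow-up.

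**The concern.** One section uses two attrition rules. The smaller, interim sample is raised for expected loss. The sample that carries the primary test is not, although the same patients, procedures and exclusions apply. If 77 per arm is the number needed for analysis, then recruiting 77 per arm falls short by whatever is lost. If 77 per arm is the number to be randomised, the power attached to it is the power for a trial without losses.

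At stake is whether the statement of 80% power is true of the trial as it will be recruited. The shortfall is a few percentage points. It matters because the plan itself expects loss and because the calculation has almost no slack to absorb it.

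**Working it through.** **Inputs (all from section 2.6).** One-sided α = 0.05 (z = 1.645); power 80% (z = 0.842); margin 0.05; leak rates 0.18 and 0.30; true difference 0.12 in favour of the 3-row arm; allocation 1:1; 10% probability of leaving, stated for the interim sample.

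**Step 1. Reproduce the plan's figure.** With the unpooled normal approximation,

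n per arm = [p₁(1 − p₁) + p₂(1 − p₂)] × (z₁₋α + z₁₋β)² / (margin + advantage)²

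- Variance sum: 0.18 × 0.82 + 0.30 × 0.70 = 0.1476 + 0.2100 = 0.3576.
- Denominator: (0.05 + 0.12)² = 0.17².
- n = 0.3576 × (1.645 + 0.842)² / 0.17² = 76.5, so 77 per arm and 154 in total.

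This matches the printed figure exactly, with no allowance for loss. One-sided 0.025 gives 98 per arm and does not match. The match needs the 3-row arm to have the lower rate, that is 2-row 30% and 3-row 18%.

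**Step 2. Power at n evaluable patients per arm.** Power = Φ(0.17/√(0.3576/n) − 1.645).

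| Loss | Evaluable per arm | Power |
|---|---|---|
| none | 77 | Φ(2.495 − 1.645) = 80.2% |
| 5% | 77 × 0.95 = 73.2, taken as 73 | Φ(2.429 − 1.645) = 78.4% |
| 10% | 77 × 0.90 = 69.3, taken as 69 | Φ(2.361 − 1.645) = 76.3% |

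Exact binomial enumeration of the same confidence-limit rule gives 80.0% at 77 per arm and 76.6% at 69, so the approximation is adequate. The 5% row is an assumption of this review, to show a loss smaller than the plan's only figure.

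**Step 3. Keep all 77 per arm and assign an outcome to the 10% who leave.**

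- Leavers counted as no leak: rates 0.27 and 0.162, variance sum 0.3329, gap 0.05 + 0.108 = 0.158. Power = Φ(0.158/√(0.3329/77) − 1.645) = 77.6%.
- Leavers counted as leaks: rates 0.37 and 0.262, variance sum 0.4265, gap 0.158. Power = Φ(0.158/√(0.4265/77) − 1.645) = 68.4%.

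Both are below 80%.

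**Step 4. Recruitment number if 77 per arm is the evaluable target.**

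- The plan's interim rule is n × 1.1: 20 × 1.1 = 22. For the main sample, 77 × 1.1 = 84.7, so 85 per arm and 170 in total.
- The rule n/0.9 gives 77/0.9 = 85.6, so 86 per arm and 172 in total. For the interim it gives 20/0.9 = 22.2, so 23 per group. By comparison, 22 × 0.9 = 19.8, just under the 20 intended.

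**The case against.** **The arm rates are uncertain.** A reader might infer that 76% is the power on the plan's inputs as printed. It is not. Section 2.6 gives 18% as the centre's average and 30% as the expected rate with the 3-row device, yet describes a 12-point difference in favour of the experimental arm. Taken literally (2-row 18%, 3-row 30%), the true difference exceeds the margin and power is about 0.4%, with or without loss. With 2-row 18% and 3-row 6%, which also fits a 12-point advantage, power is about 95% and still about 93% after 10% loss, but that reading needs 44 per arm and does not reproduce 77. So 76% to 78% is conditional on the one reading that yields 154. This part of the objection stands.

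**The 10% is not stated for the primary endpoint.** It is given for the interim sample, whose follow-up is 3 months, whereas the primary window is usually 4 to 6 weeks. Loss for the leak outcome may be smaller. This also stands, and is why a range is shown.

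**Leavers are not all without an outcome.** A reader might infer that anyone who leaves before the pre-reversal X-ray contributes nothing. Section 2.4.1 has suspected leaks imaged when signs appear, and section 2.9.1 keeps data collected before exit, so a leak diagnosed earlier still counts. That limits the loss but does not remove it. A patient without symptoms who leaves before the X-ray has no ascertained status, and section 2.2 lists withdrawals and non-completers as exclusions.

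**Intention to treat covers it.** It does not. The exclusions in section 2.2 pull the other way, and under either simple assignment in Step 3 power stays below 80% with 10% leaving.

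**The article is condensed.** An enrolment target may sit in the full protocol. Even so, this article prints an attrition assumption and applies it to one of two samples in the same section, and that inconsistency is in the text at hand.

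**Conclusion.** The point holds in a limited form. The 154 is the uninflated formula result, the plan expects patients to leave, and the stated 80% power has only 0.2 points of slack. It is therefore delivered only if every randomised patient has an evaluable primary outcome.

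The shortfall is modest: about 2 points at 5% loss and about 4 points at 10%. Those sizes rest on 2-row 30% and 3-row 18%, a 5-point margin, one-sided 0.05, and leavers having no usable leak outcome. The contradictory leak rates are a separate and larger problem, and no power figure is settled until they are reconciled. The inconsistent treatment of attrition remains whichever way that is resolved.

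Two stronger readings are not supported. One is that power is definitely 76%: that figure applies a 3-month interim assumption in full to a shorter window. The other is that 172 is the required number: the plan's own interim rule gives 170.

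The abstract's wording on achieving significance is a minor matter. A sample size gives a probability of success, as section 2.6 itself expresses it.

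**What to change.** 1. Reconcile the leak rates and arm labels in section 2.6, so that any power statement has a defined basis.
2. State whether 154 is the number randomised or the number evaluable for the primary outcome.
3. If randomised, restate the power as about 76% to 78% for 10% to 5% loss, on the reading that reproduces 154. This changes one sentence and adds no patients.
4. If evaluable, state the recruitment target from a named attrition rule: 170 by n × 1.1 or 172 by n/0.9, both at 10% loss. That adds 16 or 18 patients, at a centre that section 2.1 says treats about 150 rectal cancer patients a year.
5. Use the same rule for the interim sample: 22 per group by n × 1.1, or 23 by n/0.9.
6. Align the abstract so that 154 is described as giving a stated power rather than as achieving significance.

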### Recruitment

2.7

All patients diagnosed with rectal cancer confirmed with imaging studies and colonoscopy with biopsy, assigned an elective LAR will be considered for this study. In case of matching all the inclusion criteria, and upon provision of consent form signed by the patient, or legal guardian, the patient will be asked to fill out SF-36 and QLQ-C30 questionnaires for baseline quality of life assessment. The patients will also be required to fill out the CCIS questionnaire for baseline assessment of previous incontinence.

### Assignment of interventions

2.8

#### Allocation

2.8.1

Participants will be randomly assigned to either control or experimental group with a 1:1 allocation ratio using fixed block randomization with a computerized random number generator. The block size equals at least 4 and will be unknown to the principal investigator, outcomes assessor and the operating surgeon. Because the possibility of making a stapled anastomosis will only be determined intraoperatively by the operating surgeon with respect to exclusion criteria precluding stapled anastomosis formation, all subjects will be allocated intraoperatively.

#### Blinding

2.8.2

All relevant data from patient chart except patients’ names and the stapler used during surgery will be transferred into an electronic case report form (eCRF). The eCRF should contain results of all the screening procedures, including patient history and demographics, imaging studies, bloodwork, filled-out questionnaires, operation note, and postoperative rounds during patient stay in the ICU and in the surgical ward.

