### Trial design

1.3

THREESTAPLER study is a prospective, randomized, controlled, patient and outcomes assessor blinded, uni-center, noninferiority, parallel group, 2-arm trial with 1:1 allocation ratio. Randomization will be performed using block method after intraoperative eligibility assessment.

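### Fixed blocks at a single centre, with eligibility judged by a surgeon who knows earlier allocations, leave the next allocation partly predictable

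*Protocol article*

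**What the plan says.** **Allocation.** Section 2.8.1 of the protocol article assigns patients 1:1 "using fixed block randomization with a computerized random number generator". The block size is given only as a lower bound of 4 and is concealed from the principal investigator, the outcomes assessor and the operating surgeon. Whether a stapled anastomosis is possible is settled by the operating surgeon during the operation, and therefore "all subjects will be allocated intraoperatively". Section 1.3 places randomisation after that eligibility assessment. Section 2.1 describes a single centre.

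**Blinding.** Section 1.3 calls the trial "patient and outcomes assessor blinded"; the surgeon is not claimed to be blinded. Section 2.8.2 states that all relevant chart data other than patient names and "the stapler used during surgery will be transferred into an electronic case report form". The sentence opens with an exception, so the stapler is one of the two items left out. The next sentence lists what the eCRF should contain, including "imaging studies, bloodwork, filled-out questionnaires, operation note, and postoperative rounds". It mentions no redaction of the note.

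**The concern.** Concealment of allocation has to hold up to the moment a patient is declared eligible. Here the person making that declaration is also the person who has seen which device was used before. With one block size throughout, the two arms are forced back to equality at regular intervals, so past allocations carry information about the next one.

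Some intraoperative exclusions in section 2.2 leave room for judgement: whether a total mesorectal excision with anastomosis can be done, whether an R0 resection is achievable, and whether the left colic artery can be spared. A surgeon who expects a particular device could, even without intending to, judge a difficult case differently. The intention-to-treat analysis in section 2.9.3 would not repair this, because a patient excluded before randomisation never enters it.

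A separate and smaller question is whether the assessor's blinding is secured by the text of section 2.8.2, since an operation note for a stapled anastomosis would normally identify the stapler.

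**Working it through.** **Inputs.** Number of allocations: 154, 77 per arm (section 2.6). Block size b: at least 4 (section 2.8.1). The exact value is not given, so b = 4, 6 and 8 are assumptions. The observer is assumed to know every earlier allocation.

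**The plan's own figure.** The total of 154 serves here only as a count. It reproduces with leak rates of 30% and 18%, a 12-point difference in favour of the 3-row device, margin 5%, one-sided α = 0.05 and power 80%:

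n per arm = [0.30 × 0.70 + 0.18 × 0.82] × (1.645 + 0.842)² / (0.12 + 0.05)² ≈ 0.3576 × 6.18 / 0.0289 ≈ 76.5, so 77 per arm and 154 in total.

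Which arm section 2.6 attaches each rate to is a separate matter and does not affect this point.

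**Step 1: certain allocations when b is known.** An allocation is certain once one arm has used its b/2 places in the block. For b = 4 there are six equally likely blocks. AABB and BBAA each have 2 certain positions; ABAB, ABBA, BAAB and BABA each have 1. That is 8 of 24 positions, or 1/3. Enumerating all balanced blocks for larger sizes gives values that match 2/(b + 2).

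| b | Share certain | Of 154 |
|---|---|---|
| 4 | 33.3% | 51.3 |
| 6 | 25.0% | 38.5 |
| 8 | 20.0% | 30.8 |

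**Step 2: guessing without knowing b.** The rule is to guess the arm with fewer patients so far, and to toss a coin when the arms are level. For b = 4, AABB scores 0.5 + 0 + 1 + 1 = 2.5 correct of 4, while ABAB and ABBA each score 0.5 + 1 + 0.5 + 1 = 3. The mirror-image blocks score the same, so the hit rate is (2.5 + 3 + 3)/12 = 70.8%. Full enumeration gives 68.3% for b = 6 and 66.6% for b = 8. Simulating 4,000 sequences of 154 patients gives 70.7%, 68.1% and 66.5%. Chance is 50%.

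The rule needs no knowledge of b because every completed block ends level: the arm that is behind overall is always the arm with more places left in the current block. Knowing b turns some of these good guesses into certainties but does not raise the hit rate.

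**Step 3: what varying block sizes change.** Take sizes 4, 6 and 8 with equal probability as an illustration. Weighted by the patients in each size, the lagging-arm hit rate is (4 × 0.708 + 6 × 0.683 + 8 × 0.666)/18 ≈ 68%. Varying sizes therefore remove most of the certainty in Step 1, because the observer no longer knows where a block ends, but they leave the better-than-chance guessing of Step 2 largely in place.

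**Step 4: section 2.8.2 read side by side.** The first sentence excludes the stapler from what is transferred. The second includes the operation note. The two agree if the exclusion also governs the content of the note, and conflict if the note is entered whole. The text does not say which.

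**The case against.** The safeguards in the text are real. The block size is withheld from the three roles that matter most, 4 is a lower bound and not a disclosed size, and randomisation follows the eligibility assessment. Certainty therefore requires that the surgeon infer the size. The figures also assume knowledge of the whole sequence; the number of surgeons is not given, and several who did not share information would each know less. Some exclusions, such as a T4b tumour needing multiorgan resection or a lumen too small for the stapler, are fairly concrete. All of this stands and limits the point. It does not remove it: the lagging-arm guess needs no block size, and it is available before eligibility is declared, so the order of the two steps does not prevent it.

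A reader might infer more than the documents support in three ways.

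- *That allocation is exposed to the assessor.* The stapler exclusion in section 2.8.2 can be read as covering the operation note, and nothing says that the assessor sees the whole eCRF. Access and redaction details are also what an article commonly leaves to the full protocol. That the surgeon knows the device once it is allocated is unavoidable and contradicts no claim of blinding.
- *That four steered patients equal the 5% margin.* 4/77 = 5.2 points holds only if four outcomes change, all in one arm and one direction. Steering changes the mix of risk, so the shift is 4/77 times the difference in leak risk between the patients kept and those they replaced. With an assumed difference of 10 to 30 points, that is 0.5 to 1.6 points.
- *That patients could be moved between arms.* Declaring a patient ineligible removes that patient from the trial.

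**Conclusion.** The point holds in a limited form. Fixed blocks at one centre, with an unblinded surgeon who judges eligibility immediately before allocation, make the sequence partly predictable despite the concealed size. Under the stated assumptions, about 51, 38 or 31 of 154 allocations would be certain for blocks of 4, 6 or 8 if the size were inferred, and the lagging-arm guess succeeds about 71%, 68% or 67% of the time without it. Selective exclusion before allocation is possible. The documents give no basis for estimating how often it would occur or how large a bias would follow, and none is claimed here. The operation-note wording is a secondary clarification and does not show that blinding fails.

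**What to change.** In section 2.8.1, replace the fixed block size with randomly varying sizes that are not disclosed to the site, and state that eligibility is recorded irrevocably before the allocation is revealed. The first change removes most certain predictions, though not all better-than-chance guessing. The second prevents an eligibility decision from being reversed once the arm is known.

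In section 2.8.2, state that device identifiers are removed from the operation note, and that the stapler and stapler-dysfunction fields are restricted, before any outcomes assessor has access.

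The cost is a regenerated randomisation list for patients not yet allocated, an eCRF access setting and a redaction step. Sample size, procedures and patient care are unchanged.
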